### MBSR + PAP Integration Sessions

The first Integration Sessions will occur within ≤ 48 hours of completion of the Psilocybin Session. This will be followed by two additional integration sessions. Integration sessions will consist of large group discussion and sharing of what occurred during the psilocybin session. General themes will be explored including how to integrate the psilocybin experience with daily life. Guidance will be offered regarding how subjects can continue to process their psilocybin experience.

### MBSR + PAP Follow-Up

Subjects will have the phone number of their individual therapist throughout the duration of the follow-up period, which will extend until the second set of questionnaires are administered 2 weeks following the completion of group intervention sessions. Subjects will be followed for acute suicide ideation for 28 days post-psilocybin administration and also assessed for sustained response 180 days (+/-7) post-psilocybin administration as indicated on the Schedule of Events.

# STUDY ASSESSMENTS

Every effort should be made to ensure that the protocol-required tests and procedures are completed as described. However, it is anticipated that from time to time there may be circumstances, outside of the control of the Investigator that may make it unfeasible to perform the test. In these cases, the Investigator will take all steps necessary to ensure the safety and well-being of the subject. When a protocol-required test cannot be performed, the Investigator will document the reason for this and any corrective and preventive actions that he or she has taken to ensure that normal processes are adhered to as soon as possible.

## Physical Examinations and Vital Signs

Participants will have physical examinations to include major body systems, vital signs, assessment of medical history, and weight (weight will be measured at screening only) at the time points described in the Schedule of Events. Vital signs will be monitored within 60 minutes before and 30, 60, 90, 120, 180, 240, 300, and 360 minutes after administration, which is consistent with previous studies.

Vital signs, including blood pressure, pulse rate, respiratory rate, and oxygen saturation will be also recorded at the time points described in the Schedule of Events. Vital signs will be taken prior to the administration of any investigational products at the visit.

## Adverse Events

Adverse events experienced during trial participation will be collected per the Schedule of Events and Adverse Events Section. Each study participant will be questioned about the occurrence of adverse events in a non-leading manner. Should the treating investigator feel that the adverse event is attributed to study therapy, then guidelines for subject management in Section 7.1 will be followed.

An Adverse Event (AE) is defined as any medical occurrence in a participant, including any abnormal sign (e.g., abnormal physical exam or laboratory finding), symptom, or disease, temporally associated with the participant’s involvement in the research, regardless of whether it is considered related to participation in the research. This definition includes concurrent illnesses or injuries and exacerbation of pre-existing conditions.

Events related to planned treatments or physician visits for baseline conditions collected in the medical history will not be collected, unless there is an exacerbation of the condition, in which case they will be actively followed until resolution.

The site physician will be responsible for reviewing and confirming all AEs and SAEs collected during the study. The therapy teams will collect Aes during study visits from Enrollment through Study Termination. Participants will be asked directly how they are feeling during each contact, and Aes may be captured spontaneously during psychotherapy sessions, telephone calls, or other correspondence. Completed measures may create suspicion that an AE occurred; in this case, the site staff should follow-up with the participant.

Study personnel will also assess AEs related to possible abuse of study drug or related compounds and will be trained in the identification of concerning signs of abuse.

## COVID-19 Precautionary Measures

Due to the COVID-19 pandemic, precautionary measures will be taken to ensure subject safety and trial integrity as clinically indicated and based on University of Utah Hospital and Clinics current standards.

1. As indicated per standard clinical proceedings, possible testing for all study participants and therapists within ≤ 48 hrs. of the first group session along with symptom checklist. A positive test is an exclusion.
2. Subjects and therapists will be screened for COVID-19 symptoms and possible sick contacts prior to each group/psilocybin session. The following will exclude them from participation:
   - Current symptoms of COVID-19
   - Recent positive test for COVID-19

Back up therapists will be available if a therapist is unable to participate in a session. These therapists will have completed the same training requirements.

1. As clinically indicated, group sessions will be done with social distancing (6-foot margins). During psilocybin session, subject/therapist pairs will be allowed physical contact, but not between other dyads, and only if #1 and #2 above are verified.
2. Investigators will provide pre-study education regarding the infection precautions and rationale, revisiting these throughout the group work in anticipation of the psilocybin sessions.
3. Therapists and study team will follow COVID-19 protocols as clinically indicated based on institutional policy at the time as it relates to masking.

## Monitoring for Suicide Ideation

Subjects will be monitored for acute suicide ideation after psilocybin administration. This monitoring may occur in person, by telemedicine, or over the phone. An appropriately trained and delegated Investigator will assess the subject for the occurrence of new or increased intensity of suicide ideation or suicide attempts at the time points indicated in the Schedule of Events. A clinical assessment for acute suicidal ideation will be performed following the psilocybin dosing session prior to participants leaving the site.

## Laboratory Assessments

Samples for all laboratory assessments will be drawn at the time points indicated in the Schedule of Events and when clinically indicated. All safety laboratory analyses will be performed by the local laboratory. All safety laboratory assessments must be reviewed by the treating investigator prior to study drug administration. When applicable, results from the pregnancy test must also be available for review prior to dosing. Laboratory screening will only be required for participants randomized to the MBSR + PAP arm to ensure safe and effective administration of study drug.

**Table 3: Laboratory Assessments**

| **Laboratory Assessments** | |
| --- | --- |
| **Complete Metabolic Panel** | - Sodium - Potassium - Chloride - Carbon Dioxide - Alkaline Phosphatase - Aspartate Aminotransferase - Alanine Aminotransferase - Urea Nitrogen - Glucose - Creatinine - Calcium - Protein - Albumin - Bilirubin - Anion Gap |
| **SARS-CoV-2** | - COVID-19 nasopharyngeal swab |
| **Pregnancy** | Beta-hCG Qualitative Serum at screening. Beta-hCG Qualitative Urine within 24 hours of psilocybin administration. |
| **Urine Drug Screen** | - Benzodiazepines - Barbiturates - Stimulant amines - Cocaine - THC - Opioids |

## Response Assessment

The response to study therapy will be assessed utilizing the QIDS-SR-16 and MBI-HSS(MP) at the time points indicated in the Schedule of Events. Subjects will be contacted directly by study personnel and arrangements made for the administration of the questionnaires in a consult room at the Huntsman Mental Health Institute. If necessary, telemedicine or the Storyline Health platform may be used to administer these questionnaires. In either case, the questionnaires will be filled out by an appropriately trained and delegated Investigator upon subject assessment.

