### Assess the preliminary efficacy of MBSR+PAP vs MBSR alone in reducing symptoms of depression (as measured by the QIDS-SR-16).

*Primary Endpoint:* Efficacy will be assessed through mean reduction in QIDS-SR-16 scores at 2-weeks post intervention with between-group comparison. To understand longitudinal effects, we will gather data to 6 months post intervention for both arms. Participants will be screened for eligibility with the PHQ-9 with a cut-off score of ≥ 10 required for enrollment and participants must meet DSM-5 criteria for a depressive disorder (including adjustment disorder with depressed mood).

*Primary Endpoint:* The change in depression scores as measured by the QIDS-SR-16 from enrollment to 26 weeks post-completion of the intervention (MBSR curriculum).

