## Randomization and study arm assignment

Participants who meet eligibility criteria and have consented and enrolled in the study will be randomized to either the MBSR Arm or the MBSR + PAP arm using a randomization plan generated by the SAS code, PROC plan. The study will be open label and participants will be informed as to study arm assignment prior to the first MBSR session. There will be rolling enrollment in trial participation up until the cut-off registration date prior to each MBSR course starting date. Each arm will be run independently given likely variation on numbers of participants willing to complete each study arm however efforts will be made to run both arms concurrently depending on recruitment. While the MBSR only arm can be completed on an individual basis for each participant the MBSR + PAP arm includes group-based psilocybin-assisted therapy interventions which requires 2-5 participants per MBSR cohort. We will leave open the option of running group PAP sessions for a cohort of only 2 participants however will have a goal participant number per cohort of 4 with the possibility of running up to 5 participants per cohort through this arm. To assess expectancy effects on treatment response participants will be administered expectancy scales prior to randomization to assess preference as well as post randomization to assess credibility.

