## Efficacy

The efficacy of the study therapy will be determined by the change in depression scores as measured by the QIDS-SR (primary) and burnout scores as measured by the MBI-HSS(MP) (secondary).

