**Storyline Health Assessments:**

- Patients will be notified through the Storyline app on their smartphone or smart device to complete the various study assessments. Storyline manages reminders and makes the process simple.

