**All done. Thank you.**

##### Quick Inventory of Depressive Symptomatology (Self-Report) (QIDS-SR16)

NAME: TODAY’S DATE:

Please circle the one response to each item that best describes you for the past seven days.

1. Falling Asleep:
   1. I never take longer than 30 minutes to fall asleep.
   2. I take at least 30 minutes to fall asleep, less than half the time. 2 I take at least 30 minutes to fall asleep, more than half the time.

3 I take more than 60 minutes to fall asleep, more than half the time.

1. Sleep During the Night:
2. I do not wake up at night.
3. I have a restless, light sleep with a few brief awakenings each night. 2 I wake up at least once a night, but I go back to sleep easily.

3 I awaken more than once a night and stay awake for 20 minutes or more, more than half the time.

1. Waking Up Too Early:

0 Most of the time, I awaken no more than 30 minutes before I need to get up. 1 More than half the time, I awaken more than 30 minutes before I need to get up.

1. I almost always awaken at least one hour or so before I need to, but I go back to sleep eventually.
2. I awaken at least one hour before I need to, and can’t go back to sleep.
3. Sleeping Too Much:

0 I sleep no longer than 7–8 hours/night, without napping during the day. 1 I sleep no longer than 10 hours in a 24-hour period including naps.

2 I sleep no longer than 12 hours in a 24-hour period including naps. 3 I sleep longer than 12 hours in a 24-hour period including naps.

Enter the highest score on any 1 of the 4 sleep items (1–4 above)

1. Feeling Sad:
2. I do not feel sad
3. I feel sad less than half the time. 2 I feel sad more than half the time. 3 I feel sad nearly all of the time.
4. Decreased Appetite:
5. There is no change in my usual appetite.
6. I eat somewhat less often or lesser amounts of food than usual. 2 I eat much less than usual and only with personal effort.

3 I rarely eat within a 24-hour period, and only with extreme personal effort or when others persuade me to eat.

1. Increased Appetite:
2. There is no change from my usual appetite.
3. I feel a need to eat more frequently than usual.
4. I regularly eat more often and/or greater amounts of food than usual. 3 I feel driven to overeat both at mealtime and between meals.
5. Decreased Weight (Within the Last Two Weeks): 0 I have not had a change in my weight.

1 I feel as if I’ve had a slight weight loss. 2 I have lost 2 pounds or more.

3 I have lost 5 pounds or more.

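### The protocol has a delegated investigator fill out the self-report QIDS-SR-16 and MBI-HSS(MP), which contradicts the instruments and allows avoidable rater influence in an open-label trial

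*Protocol*

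**What the plan says.** Section 10.6 (Response Assessment) names the QIDS-SR-16 and the MBI-HSS(MP) as the measures of response. They are to be administered in a consult room or, if necessary, by telemedicine or on the Storyline platform. For all of these routes it adds that "the questionnaires will be filled out by an appropriately trained and delegated Investigator upon subject assessment".

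The QIDS-SR-16 carries the primary efficacy question. Section 1.1 defines the endpoint as "mean reduction in QIDS-SR-16 scores at 2-weeks post intervention with between-group comparison", and section 11.2 lists the QIDS as primary and the MBI as secondary.

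Other places describe these scales differently:

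- The QIDS appendix is the self-report version. It tells the respondent: "Please circle the one response to each item that best describes you for the past seven days".
- The MBI appendix consists of first-person statements about the respondent's own work and feelings.
- The first secondary objective (section 1.2) describes the burnout symptoms as reported by the participant.
- Section 5.1 requires enough reading literacy to understand the study questionnaires.

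On blinding, section 9.2 states: "The study will be open label and participants will be informed as to study arm assignment". No section describes a blinded or independent assessor.

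**The concern.** A self-report scale records the participant's own choice of answer. If an investigator fills it out after assessing the participant, a second person's judgement can enter the score. In an open-label trial that person probably knows whether the participant received psilocybin.

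The participant's own knowledge of the arm cannot be removed here, but the recorder's influence can. It also cannot be repaired in the analysis, because it arises when the data are collected. Section 12.2 (Statistical Power) gives estimation of effect sizes for larger trials as a main goal of the pilot. A shift from recording would therefore carry over into the planning of those trials.

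The contradiction has a second consequence. Staff who follow section 10.6 and staff who follow the printed form would collect the primary endpoint in different ways. Nothing requires the same mode at baseline, week 11 and week 33.

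**Working it through.** **Text check.** The claim rests on no stated figure, so the passages are set side by side.

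| Question | Section 10.6 | Elsewhere in the protocol |
|---|---|---|
| Who fills out the QIDS-SR-16? | A delegated investigator, by every route | The respondent (QIDS appendix) |
| Who fills out the MBI-HSS(MP)? | A delegated investigator, by every route | First-person items (MBI appendix); participant as the source (section 1.2) |
| On what basis? | An assessment of the participant | The participant's own reading of each item (both appendices; literacy criterion, section 5.1) |
| Does the recorder know the arm? | Not stated | Open label (section 9.2); no blinded assessor anywhere |

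Section 10.6 is also hard to follow on its own terms. It allows Storyline, which section 2.2 describes as a platform for assessments done by participants on their own device, yet it still has the investigator fill out the form.

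**Does the recorder know the arm?** This is an inference. Section 2.1 (Clinical Experience) places a lead study monitor at every dosing session, and section 6.1 (The Psilocybin Session) identifies that monitor as one of the principal investigators. Some investigators therefore know the allocation. The protocol does not say who is delegated to record the scales, and it excludes no one.

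**Illustration of size, on an assumed bias.** The inputs are:

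- From the protocol: 12 per arm (section 4.2); alpha 0.05, ICC 0.5 and d = 1.0 (section 12.2).
- Assumed: no true effect, a two-sided two-sample t test on change with 22 degrees of freedom, and a recording shift *b*, in SD units, that differs between arms and falls on the change score.

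At ICC 0.5 the SD of change is √(2 × (1 − 0.5)) = 1 raw SD, so *b* and d are on the same scale. The noncentrality is *b* / √(2/12) = *b* / 0.408.

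| Assumed *b* | Noncentrality | Two-sided rejection rate | *b* as share of d = 1.0 |
|---|---|---|---|
| 0 | 0 | 5.0% | 0% |
| 0.1 | 0.24 | 5.6% | 10% |
| 0.2 | 0.49 | 7.6% | 20% |
| 0.3 | 0.73 | 10.8% | 30% |
| 0.5 | 1.22 | 21.6% | 50% |

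The protocol has no value for *b*. The table shows what each assumption would imply and says nothing about which one applies.

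**The case against.** The best case for the protocol runs as follows.

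- **Filling out may mean transcription.** The QIDS has fixed, worded response options, and an investigator may only be copying down the participant's choices. This is possible, but no section limits the investigator to it, and tying the act to an assessment of the participant points the other way. The ambiguity itself needs resolving.
- **Both arms are handled alike.** A footnote to Table 2 calls for questionnaires to be assessed similarly across arms. A recording effect common to both arms cancels in the contrast, so only a differential effect matters. Similar procedures do not exclude one when the recorder knows the arm.
- **Participants know their arm in any case.** This stands. Self-completion removes the recorder's influence and leaves participant expectancy untouched.
- **This is a 24-person pilot.** This also stands, and it limits how serious the point is.

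A reader might infer three stronger things that the documents do not support.

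1. *The recorder delivers the treatment.* Section 10.6 requires only training and delegation. MBSR is led by course staff (sections 6.1 and 9.3), and the psilocybin session is run by assigned therapists with a lead therapist. Nothing says that these people record the scales.
2. *The Storyline text flatly contradicts section 10.6.* The statement "Patients will be notified through the Storyline app on their smartphone or smart device to complete the various study assessments" stands in the exploratory Storyline part of section 12.2, and Table 2 lists the Storyline questionnaires in a separate block from the QIDS and MBI. It may not cover these two scales. The firm conflict is with the instruments and section 1.2.
3. *The primary outcome has become an unblinded interview rating with a known inflation of the error rate.* The text permits such a rating without establishing it, and the size is assumed.

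**Conclusion.** The contradiction is certain: section 10.6 assigns to an investigator two scales that the appendices and section 1.2 treat as the participant's own report. The risk of bias is a reasonable inference. It rests on the open-label design, on the absence of any blinded assessor, and on reading section 10.6 as it is written.

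Its size is unknown. The false-positive rates of 5.6% to 21.6% depend entirely on an assumed differential shift of 0.1 to 0.5 SD and are not evidence of severity.

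This should be fixed, because it concerns how the primary endpoint is collected, cannot be undone afterwards and takes little to change. It does not by itself invalidate the trial. It covers the QIDS-SR-16 and the MBI-HSS(MP), the only scales that section 10.6 names.

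**What to change.** Replace the last sentence of section 10.6 with wording such as:

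> Participants complete the QIDS-SR-16 and the MBI-HSS(MP) themselves, on paper or electronically. The same mode is used at baseline, week 11 and week 33 in both arms where possible, and the mode is recorded. Staff may administer the forms, check completeness, transcribe paper answers unchanged, and review completed forms for the safety follow-up in section 10.2. They may not score an item, interpret a response or alter a response on the participant's behalf.

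The permission to review must stay in. Section 10.2 relies on completed measures to prompt follow-up of possible adverse events, and the QIDS contains an item on death and suicide. A ban on staff reading or entering answers would conflict with that process and make paper forms unworkable.

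Then reconcile section 1.2, section 10.6, the Storyline Health Assessments text in section 12.2 and the QIDS appendix, so that each says the same about who completes which scale.

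The cost is small: one sentence and a field for the mode. Remote participants need a self-completion route. Section 10.6 already allows Storyline for these scales. REDCap is named only for consent (section 9.1), so its use for questionnaires would have to be added if wanted.

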# CRITERIA FOR EVALUATION AND ENDPOINT

## Safety

Routine safety and tolerability will be evaluated from the results of reported signs and symptoms, scheduled physical examinations, vital sign measurements, and clinical laboratory test results. More frequent safety evaluations may be performed if clinically indicated or at the discretion of the investigator.

## Efficacy

The efficacy of the study therapy will be determined by the change in depression scores as measured by the QIDS-SR (primary) and burnout scores as measured by the MBI-HSS(MP) (secondary).

## Stopping Rules

For 14 days following psilocybin administration, subjects will be monitored for adverse events. Study will be placed on hold and the study will be reevaluated if there is an occurrence of any grade 3 (or above) adverse event attributed to psilocybin in the first cohort of participants. These include hypertensive emergency or other serious cardiac events and other need for hospitalization attributed to psilocybin administration. For 28 days following psilocybin administration, subjects will be monitored for acute suicide ideation and suicide attempt. Any suicide attempt throughout the trial will also preclude further enrollment. Any attempt whether completed or not will be recognized as a serious adverse event and warrant study closure. Subjects’ physical and psychiatric states will be closely followed throughout the trial and for 28 days after psilocybin administration. If neither stopping rule is met, then the study will open for continuation. There will be no further administrations of study drug within this 28 day window. If the stopping rule is reached prior to the end of enrollment, the analyses will still be performed for those patients who have completed treatment prior to the time the stopping criterion is reached. In this case, the statistical power for the analyses may be reduced.

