## Duration of Therapy

*MBSR arm*: Total duration of the MBSR curriculum is 8 weeks with a once weekly session (over Zoom or in person) for 2 hours and a full day mindfulness retreat.

*MBSR + PAP arm*: Total duration is the same as above for the MBSR curriculum with a 9 week total duration (given additional integration session following MBSR completion). This arm will include an additional time to incorporate the PAP protocol. This includes three 90min preparatory sessions, one 8 hour psilocybin session (in place of the MBSR retreat), and three 90 minute integration sessions.

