# STATISTICAL CONSIDERATIONS

## Population for analyses

12.1.1 Safety Data Set. All participants enrolled in the trial will be eligible for the safety data set. AEs and suicidality per C-SSRS will be assessed across both study arms.

12.1.2. Evaluable for intent-to-treat (ITT) analysis. All participants enrolled in the trial and randomized to either MBSR + PAP or MBSR only will be eligible for the (ITT) analysis. The primary analysis will involve intention to treat analyses on all study outcomes.

12.1.2 Evaluable for per-protocol analysis. Participants in the MBSR arm who have completed two-thirds of the MBSR sessions will be considered evaluable for the per-protocol efficacy data set. Participants in the MBSR + PAP arm who have completed two- thirds of the MBSR sessions (excepting the MBSR retreat) *as well as* two out of three of the preparatory sessions, the psilocybin therapy session, two out of the three integration sessions, and a baseline and post-psilocybin QIDS-SR and MBI will be considered evaluable for the per-protocol efficacy data set.

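### The early-stop sentence in Section 11.3 sets a completers-only analysis that conflicts with the ITT and safety sets of Section 12.1, and could leave no first-cohort psilocybin participant in the analysis

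*Protocol*

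**What the plan says.** Section 11.3 (Stopping Rules) has two triggers. One is "any grade 3 (or above) adverse event attributed to psilocybin in the first cohort of participants", with this window: "For 14 days following psilocybin administration, subjects will be monitored for adverse events". The other is any suicide attempt, with suicidality followed for 28 days after dosing. The section then fixes what is analysed. The condition is "If the stopping rule is reached prior to the end of enrollment"; the consequence is that "the analyses will still be performed for those patients who have completed treatment prior to the time the stopping criterion is reached". The next sentence adds that power may be lower.

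Section 12.1 (Population for analyses) defines the sets without reference to stopping. For safety: "All participants enrolled in the trial will be eligible for the safety data set". For efficacy: "All participants enrolled in the trial and randomized to either MBSR + PAP or MBSR only will be eligible for the (ITT) analysis". It makes ITT the primary analysis for every outcome.

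On timing, Table 2 (Section 8) puts the psilocybin session in week 7 and the integration sessions in weeks 7 to 9. Sections 4.4 and 6.4 give a nine-week therapy period; Section 6.4 explains that one integration session in the combined arm follows the end of the MBSR course. Section 6.1 allows the psilocybin session to move by a week either way.

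**The concern.** The protocol names two analysis populations for the same situation. The one in Section 11.3 depends on how far participants had got when an adverse outcome occurred, so membership is decided after randomisation and partly by the outcome itself. Because participants are dosed in groups and share an integration schedule, one event can take out the whole group.

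Safety is a primary objective, and the first cohort is the one that the grade 3 rule watches. If its members drop out of the analysed sample because one of them had a qualifying event, the between-arm contrast cannot be estimated, and under the Section 11.3 wording the safety summary has no dosed participant in it. If the conflict is left open, the population would have to be chosen after a safety stop, with the events known.

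The stop sample also matches none of the sets in Section 12.1. The per-protocol set there asks for two of three integration sessions, whereas completing treatment may mean all three. The stop sample could thus be narrower than per-protocol.

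**Working it through.** No figure in the protocol bears directly on this point, so the check is date arithmetic.

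**Inputs.** Table 2 numbers week 2 as days 8–14 and week 3 as days 15–21. Continued, week 7 is days 43–49, week 8 is days 50–56 and week 9 is days 57–63. Cohort size is 2 to 6 (Sections 4.1 and 6.1; Section 9.2 has up to 5, with a goal of 4). Assumptions: the last integration session stays in week 9 when the psilocybin session moves, and the last MBSR class is in week 8.

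**Formula.** Shortest gap = first day of the later week − last day of the dosing week. Longest gap = last day of the later week − first day of the dosing week. Nominal case, dosing to last integration session: 57 − 49 = 8 and 63 − 43 = 20; with the same weekday, 14.

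| Psilocybin session | Dosing day | Days to last integration session (week 9) | Days to last MBSR class (week 8) |
|---|---|---|---|
| A week early | 36–42 | 15–27 | 8–20 |
| Nominal, week 7 | 43–49 | 8–20 (same weekday 14) | 1–13 (same weekday 7) |
| A week late | 50–56 | 1–13 | −6 to 6 |

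**Against the stopping windows.** On the nominal same-weekday schedule, the whole 14-day adverse event window falls no later than the last integration session, as do the first 14 of the 28 suicidality days. A week early, the gap always exceeds 14 days. A week late, it is always shorter, so some of the window falls after completion.

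**Who remains after a first-cohort trigger (nominal, same weekday, day 0 = dosing):**

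| Trigger | First psilocybin cohort | MBSR-only participants on the same course |
|---|---|---|
| Days 0–6 | not complete: 0 of 2–6 analysed | not complete: also excluded |
| Days 7–13 | not complete: 0 of 2–6 analysed | complete: retained |
| Either, under Section 12.1 | all 2–6 in the safety and ITT sets | all in |

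Nobody has been dosed before the first cohort, so no other psilocybin participant can fill the gap. Section 15.3 points the same way: a participant with an unexpected or serious adverse event is withdrawn, so one whose event precedes week 9 would not go on to complete treatment.

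**Is the enrolment condition met?** Usually, for a first-cohort trigger: Section 4.1 pauses accrual after the first four patients have been enrolled and treated.

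**Scale of the power remark.** Power = Φ(d / (sd·√(2/n)) − 1.96), with d = 1.0 and n per arm. The stated 81% is matched at n = 12 by sd = √0.75 = 0.866 (my assumption; it fits a baseline-adjusted follow-up at ICC 0.5): 1/(0.866 × 0.408) = 2.83, and Φ(0.87) = 80.7%. The same formula gives 63.7%, 51.6%, 37.2% and 21.0% at 8, 6, 4 and 2 per arm. With no psilocybin participant there is no contrast at all, which is more than reduced power.

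**The case against.** The strongest reply is that the sentence only assures the reader that a stop does not cancel the analyses. It does not say that others are excluded, and Section 12.1 stands without exception. This is partly right: exclusivity is a reading, not the wording. But the following remark on reduced power makes sense only if the sentence fixes the analysed sample, so the two sections still need reconciling.

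Four stronger conclusions are tempting, and the documents do not support them.

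- *That the rule drops the psilocybin arm and keeps the comparator.* Until the last MBSR class, concurrent MBSR-only participants are incomplete too. A dosing-day event removes both concurrent groups. The comparator is retained only for later triggers, or through earlier MBSR courses, since Section 9.2 runs the arms independently. Sections 6.1 and 9.3 also mention nine weekly classes, so even the week 8 finish is not settled.
- *That safety data on dosed participants would be lost.* Adverse events are still tracked under Section 12.2, and serious events are collected and reported under Sections 15.5 and 15.6. What is at risk is the analysed sample, not collection or reporting.
- *That exclusion is certain.* Completion is undefined. The study summary describes a one-time administration, so a dosed participant might be counted as treated, although Sections 4.4 and 6.4 describe nine weeks of therapy. A late session, or a suicide attempt after the last integration session, would also leave the cohort as completers.
- *That everyone must continue to the week 11 and week 33 visits.* Section 8 applies the schedule to the entire study, Section 11.3 speaks of study closure after a suicide attempt, and Section 15.3 withdraws participants with serious events. These conflict, and a review of the analysis set cannot choose between them.

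It is also fair that the grade 3 rule leads to a hold and re-evaluation rather than termination, and that efficacy power after a first-cohort stop is low even with everyone kept (37.2% at 4 per arm).

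**Conclusion.** The concern holds as a contradiction between Sections 11.3 and 12.1 with a potentially biasing consequence. On the nominal schedule, a first-cohort trigger in the 14-day window would usually precede completion and could leave 0 of 2–6 dosed participants in the analysis, against all of them under Section 12.1. This rests on reading the sentence as exclusive, on completion meaning the full course to week 9, on a session held at or near week 7, and on the stop coming before enrolment ends. The documents give no probability that a rule will be triggered. The stopping criteria themselves are not in question. The change should be made, because settling the population after a safety stop would be post hoc.

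**What to change.** Replace the analysis sentence in Section 11.3 with:

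> If the stopping rule is reached, all enrolled participants remain in the safety set and all randomised participants in the ITT set defined in 12.1, using all data collected; an analysis of participants who completed treatment before the stop is supplementary.

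State what completing treatment means for that supplementary analysis. The remark on reduced power can stay.

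Separately, reconcile Sections 8, 11.3 and 15.3 on whether scheduled follow-up assessments continue after a stop. This affects the data available: the first QIDS-SR-16 after treatment is in week 11, so even recent completers could lack the primary outcome.

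The analysis change is wording only. The mixed model with maximum likelihood in Section 12.2 is already intended to handle incomplete data. The small downside is that the ITT estimate after a stop includes partly treated participants.
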